## Abstract

**Introduction:**

The major pathophysiological symptom of the menopause affecting daily life is hot flushes, which are also associated with elevated cardiovascular disease risk. A hot flush is a sudden and intense heat sensation causing skin flushing and profuse sweating. Menopause-induced oestrogen deficiency could increase the sensitivity of skin blood vessels and sweat glands in postmenopausal women, which could result in more frequent and larger increases in skin blood flow in postmenopausal women consistent with hot flushes. Furthermore, oestrogen withdrawal could also alter the structure of the skin blood vessels and/or sweat glands which may also contribute to hot flushes. This trial aims to examine the function and structure of skin blood vessels and sweat glands in premenopausal and postmenopausal women.

**Methods and analysis:**

This is a single-centre multi-cohort observational study. Participants will attend the laboratory at Liverpool John Moores University (LJMU) on two separate occasions, ∼7 days apart. Visit 1 will consist of anthropometry, a blood sample and assessment of post-ganglionic skin blood vessel and sweat gland responsiveness via cutaneous microdialysis. At visit 2, participants will return for a skin punch biopsy. A between groups statistical analysis of the pre- and postmenopausal cohorts will be conducted in a blinded manner.

**Ethics and dissemination:**

The trial was approved by the North West - Greater Manchester South Research Ethics Committee (22/NW/0300) in the UK. The study adheres to The Declaration of Helsinki and is being conducted in accordance with the UK Policy Framework for Health and Social Care Research.

**Discussion:**

Identifying functional and/or structural changes in skin blood vessels or sweat glands in women with hot flushes would increase our understanding of their cause(s) and side effects, and help to design effective treatments, including interventions that can manipulate the activity of the skin blood vessels and/or sweat glands via pharmacological or non-pharmacological methods.

**Trial registration numbers:**

NCT06222073.

## Introduction

Menopause marks a crucial milestone in a woman's life and signals the end of the reproductive life cycle, usually occurring between the ages of 45 and 55 years. The cessation of oestrogen production has a direct effect on various organs in the body and women commonly experience wide-ranging menopausal symptoms, including sleep disturbance, bone loss, brain fog, weight gain, anxiety, depression and fatigue. Hot flushes (or vasomotor symptoms), the major pathophysiological symptom of the menopause, are experienced by ∼80% of women for up to several years (1) and can have a profoundly negative impact on quality of life (2, 3). A hot flush is an extreme thermoregulatory event, characterised by a sudden and intense feeling of heat, skin flushing/reddening and profuse sweating that can be triggered by environmental factors, such as heat stress, alcohol, caffeine and emotional stress, but often hot flushes occur spontaneously. The severity of hot flushes is associated with vascular dysfunction and increased cardiovascular disease risk through changes in cardiometabolic function (3, 4).

Hormone replacement therapy (HRT) can alleviate hot flushes, but is not suitable for all individuals, such as those with a medical history of hormone-receptive cancer, and HRT can also experience poor uptake due to historic links with breast cancer and an increased risk of cardiovascular disease (5). Fezolinetant, a non-hormonal neurokinin-3-receptor (NK_3_R) antagonist that dampens central thermoregulatory mechanisms associated with moderate to severe vasomotor symptoms, has recently been licensed for private prescription in the UK, but is not yet widely available. Few alternative treatments are available and consequently, many females suffer the debilitating symptoms of hot flushes due to a lack of therapies, and, ultimately, an incomplete understanding of the physiological mechanisms underpinning hot flushes.

The skin contains a vast array of neural, vascular and morphological structures and plays a crucial role in thermoregulation (6). The key events of a hot flush occur at the skin, namely, flushing/reddening and sweating. Elevations in skin blood flow and sweating include a series of inter-related steps (e.g., function) involving blood vessels and sweat glands (e.g., structure). Vasodilatory neurotransmitters or local substances bind to receptors on the skin blood vessels and sweat glands in order to cause vasodilation (increase in skin blood flow) and the release of sweat (7, 8). Previous work suggests that the increase in skin blood flow during a hot flush is initiated by elevations in neurotransmitters of vasodilator nerves (9) and nitric oxide (10). Other researchers have shown that calcitonin gene-related peptide (CGRP), a potent skin vasodilator (11, 12), is increased in the blood during hot flushes (13, 14). Oestrogen deficiency reduces levels of nitric oxide and CGRP (15, 16), possibly affecting skin blood vessel receptor sensitivity to these substances in postmenopausal women, potentially inducing more frequent and larger increases in skin blood flow consistent with hot flushes. Furthermore, women who experience hot flushes have enhanced skin blood flow responses to vasodilators (at the endothelium and smooth muscle) (17–19). Thus, skin blood vessels of symptomatic postmenopausal women might be overly sensitive to vasoactive substances that contribute to hot flushes, and the effect of oestrogen withdrawal on sweat gland receptors, and any potential alteration in their sensitivity, is also unknown.

The skin undergoes many morphological changes with advancing age (e.g., reduced collagen content and elasticity) which is accelerated with oestrogen withdrawal, resulting in reductions in collagen content, elasticity, water content and thickness (20). It is unknown if hypo-oestrogenism affects key vascular, sudomotor and/or neural structures in the skin, which also play a role in hot flushes. The number of sweat glands is generally constant across the lifespan in healthy individuals, but they are sensitive to repeated or a lack of stimuli. More specifically, the size of sweat glands and the number and density of the sympathetic nerve endings surrounding sweat glands can reduce as a result of decreased use (21). Similarly, the number of skin blood vessels can decrease with aging (22, 23), as they are also sensitive to repeated (or lack of) stimuli (24) leading to a reduction in both number and size when there are no recurring elevations in blood flow.

It is currently unknown whether the structure of skin blood vessels and/or sweat glands is affected by menopause or if they contribute to the occurrence of hot flushes. Furthermore, it remains uncertain whether there is a relationship between the function of skin blood vessels and/or sweat glands and the occurrence of hot flushes.

### Study aims

The overall aim of the study is to assess both function and structure of skin blood vessels and sweat glands in premenopausal and postmenopausal women. The specific objectives are:
1.To assess the responsiveness of skin blood vessels and sweat glands in premenopausal women and postmenopausal women with and without hot flushes.2.To examine the structure of skin blood vessels and sweat glands in premenopausal women and postmenopausal women with and without hot flushes.

## Methods and analysis

### Study setting and recruitment plan

Recruitment (*n* = 36) will take place in the UK, commencing October 2024 for 12 months. The trial will end (last data collection from the last participant) in October 2025. A participant information sheet (PIS) will be given to potential participants, who will be recruited through local advertisement, social media websites and via lead members of local menopause support groups sharing the study information with their members.

### Sample size calculation

Based on previously reported differences in post-ganglionic skin blood flow responses between postmenopausal women with and without hot flushes (17–19), a power (1-β) of 0.9 and an effect size of 1, 24 postmenopausal women (12 who experience hot flushes and 12 who do not) and 12 premenopausal women will be recruited for this study.

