### Experimental design

This is a parallel group design where participants will attend the laboratory on two separate occasions. The first visit will consist of anthropometric measurements and a blood sample, followed by assessment of post-ganglionic skin blood vessel and sweat gland responsiveness (cutaneous microdialysis). At the second visit (∼7 days later), participants will undergo a skin punch biopsy.

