**Figure 1 F1:**
[figure not shown]
Illustration of the microdialysis technique and apparatus. Created in BioRender. [name] (2025). https://BioRender.com/ouwrev6.

Following microdialysis membrane placement and allowing for its associated hyperaemic response to subside (≥90 min), baseline CVC and SR will be collected for 5 min. Each membrane will subsequently be randomly assigned and perfused with one of the following: increasing doses of CGRP (1 × 10^−11^–10^−4^; 8 doses at 10-fold increments) dissolved in Ringer's solution, acetylcholine (Ach; 1 × 10^−7^-1M; 8 doses at 10-fold increments) dissolved in Ringer's solution, or sodium nitroprusside (SNP; 1 × 10^−7^-50 mM; 8 doses at 10-fold increments) dissolved in Ringer's solution. Each dose will be administered for 7 min (1 min at a perfusion rate of 5 µl/min and 6 min at 2 µl/min). Following the last dose, 50 mM SNP will be perfused through each membrane for 10 min to initiate peak vasodilation at each of the assessed sites (29).

Data will be continuously sampled at 50 Hz (PowerLab, ADInstruments, Oxford, UK) and recorded online (LabChart, ADInstruments, Colorado Springs, Colorado, USA). For each dose, CVC and SR will be averaged at 10 s intervals, and the 60 s average around the maximum 10 s value from each stage will be selected for analysis (29).

A between groups statistical analysis of the pre- and postmenopausal cohorts will be conducted in a blind manner. Exploratory analyses using a linear mixed model with fixed effects of drug dose (cutaneous microdialysis) and/or group will be conducted. Dose-response curves for CVC and SR at each of the three microdialysis sites will be constructed using a nonlinear fitting technique, from which the effective concentration causing 50% of the maximal response (EC_50_) will be identified (Prism, GraphPad Software). *Post hoc* comparisons across drug doses or between groups will be completed using Bonferroni adjusted LSD. Effect estimates with a 95% confidence interval for differences between groups, as well as changes within groups over drug doses, will be reported.

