### Study withdrawal

Each participant has the right to withdraw from the study at any time with no obligation to provide a reason. If provided, reasons for withdrawal will be retained, but personal data will be disposed of. Furthermore, participants may be withdrawn from the study by the research team at any time if the research team considers it necessary for any reason including:
•Ineligibility (either arising during the study or retrospectively having been overlooked at screening).•Significant non-compliance with study requirements.•Withdrawal of consent.Withdrawal from the study will not result in exclusion of the participant's data from analysis, as all data will be pseudonymised. Withdrawn participants will not be replaced. Participants will be asked for their reasoning behind withdrawal, either via email or telephone call and the reason will be recorded in an end of study case report; participants are able to give no reason for withdrawal.

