### Study limitations

Whilst this protocol has been designed to comprehensively evaluate the function and structure of skin blood vessels and sweat glands in postmenopausal women, there are some limitations to the study. Firstly, being an observational study, it does not allow causal conclusions to be drawn between menopause, hot flushes and any changes in skin function and/or structure. Rather, causal relationships will require investigation through longitudinal and/or intervention studies. Secondly, as the sample size is relatively small (*n* = 36), statistical power may be limited, particularly in detecting small differences between groups. Furthermore, recruitment from a single geographical area in the U.K. may mean that findings are not generalisable to the wider population or across ethnic groups. Participants will subjectively report hot flush incidence and severity using a 7-day diary (25) which may be susceptible to perception and/or reporting bias. However, the questionnaire is validated, demonstrating good reliability and consistency against controlled studies. The skin punch biopsy will provide important information about skin structure, yet the single forearm biopsy means that any morphological changes in this limited area, will not necessarily reflect systemic changes in skin structure. Finally, single-time sampling means that measurements will not allow for potential subtle changes according to diurnal rhythms, or hormonal fluctuations, which are beyond the scope of this study.

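### Wrong as written: for two independent groups of 12 at a conventional alpha, an effect size of 1 does not give the stated power of 0.9 (about 0.65 two-sided, 0.77 one-sided, if the effect size is a standardised mean difference)

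*Protocol article*

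**What the plan says.** The Sample size calculation section takes as its basis previously reported "differences in post-ganglionic skin blood flow responses between postmenopausal women with and without hot flushes". It then gives "a power (1-β) of 0.9 and an effect size of 1, 24 postmenopausal women (12 who experience hot flushes and 12 who do not", and adds 12 premenopausal women. It gives no alpha, sidedness, test or effect-size metric, and does not tie the figure to a particular outcome variable.

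Four other places bear on how the figure should be read:

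- Experimental design: "This is a parallel group design where participants will attend the laboratory on two separate occasions".
- The statistical paragraph for Visit 1 plans a linear mixed model with dose and/or group as fixed effects, described as exploratory. It also plans EC50 from fitted dose-response curves and 95% confidence intervals, and says that post hoc "comparisons across drug doses or between groups will be completed using Bonferroni adjusted LSD".
- Study withdrawal: "Withdrawn participants will not be replaced".
- Study limitations: "statistical power may be limited, particularly in detecting small differences between groups".

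**The concern.** The sample size section fixes the comparison (two sets of different women), the group sizes (12 and 12), the effect size (1) and the power (0.9). Only alpha and the test are open, and no usual choice of these for two independent groups makes the four figures agree. This is therefore not a detail that an article may leave to the full protocol: a printed result does not follow from the printed inputs.

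At stake is how a null result would be read. A reader who relies on 0.9 will think a true 1 SD difference had a 10% chance of being missed. Under the two-sided t-test reading that chance is about 35%, and under the one-sided reading about 23%. The limitations section does not correct this, because its emphasis is on small differences, whereas the shortfall is at the large difference the study was designed around.

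**Working it through.** **Inputs from the protocol article:** n = 12 per group, effect size 1, power 0.9 (Sample size calculation); independent groups (Experimental design).

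**Assumptions:** the effect size is a standardised mean difference d; the test is a two-sample t-test; alpha is 5% two-sided, consistent with the planned 95% confidence intervals. One-sided variants are shown as the range.

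**Step 1, the stated figure.** With n per group, the degrees of freedom are 2n − 2 and the noncentrality is d × √(n/2). For n = 12 and d = 1:

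- degrees of freedom = 22; noncentrality = √6 = 2.449
- two-sided 5%: critical t = 2.074, power = 0.649, miss risk = 1 − 0.649 = 0.351
- one-sided 5%: critical t = 1.717, power = 0.767, miss risk = 0.233
- one-sided 10%: critical t = 1.321, power = 0.869

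The stated 0.9 is not reproduced. Reaching it at 12 per group would need alpha of about 0.26 two-sided or 0.13 one-sided.

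**Step 2, what would give 0.9.**

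- Group size for d = 1, two-sided 5%: n = 22 gives 0.8997 and n = 23 gives 0.912, so 22 to 23 per group.
- Group size for d = 1, one-sided 5%: n = 18 gives 0.902.
- Detectable difference at 12 per group, two-sided 5%: d = 1.385, rounded to 1.39.

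**Step 3, other readings of the same sentence.**

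- Effect size as Cohen's f = 1: 0.997 for two groups and above 0.999 for three groups. This overshoots 0.9.
- Three-group one-way ANOVA, N = 36, largest gap 1 SD: f = 0.408 (third group midway) gives 0.54; f = 0.471 (third group equal to one of the others) gives 0.67.
- All postmenopausal against premenopausal, 24 vs 12, d = 1, two-sided 5%: 0.785. This is not the comparison the section cites.
- Paired or one-sample t-test, d = 1: n = 12 gives 0.883 and n = 13 gives 0.911. This is close to 0.9 but does not apply to different women.

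**Step 4, repeated measures.** Suppose each woman's response is averaged over m = 8 doses with a common within-woman correlation ρ, and the gap is 1 SD at every dose. For two groups with N = 24 and f = 0.5, the noncentrality of the between-group F test is λ = f² × N × m / (1 + (m − 1)ρ) = 48 / (1 + 7ρ), on 1 and 22 degrees of freedom:

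- ρ = 0.3: λ = 15.48, power 0.964
- ρ = 0.4: λ = 12.63, power 0.924
- ρ = 0.45: λ = 11.57, power 0.901
- ρ = 0.5: λ = 10.67, power 0.877
- ρ = 0.7: λ = 8.14, power 0.778
- ρ = 0.8: λ = 7.27, power 0.732

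This route reaches 0.9 when ρ is about 0.45 or less. The article gives no ρ.

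**Step 5, illustrations only.** Both start from the two-sided 5% t-test at d = 1. If alpha were divided by three for three group pairs, power at 12 per group would be 0.459. If two women per group were lost, power at 10 per group would be 0.562. The article fixes neither the Bonferroni family for this contrast nor a dropout rate.

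**The case against.** The strongest objection is that 0.65 rests on inputs the article does not state. Alpha, sidedness, test and metric are all supplied here, and the unseen full protocol may hold them. That stands as a limit on the number: a reader might infer that the true power simply is 0.65 with a 35% miss risk, and the article does not support so definite a figure. It does not restore 0.9, since even a one-sided 10% test falls short.

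The second objection is that the blood flow outcome is measured at eight doses in each woman and a mixed model is planned, so a repeated-measures calculation may lie behind the figure. This stands in part. A reader might infer that averaging over doses cannot rescue 0.9; that would be wrong, as Step 4 shows. A three-group version at ρ = 0.5 gives 0.907 if f = 0.471, though 0.80 if f = 0.408. But the article does not say that such a calculation was made, and it calls the mixed model exploratory. The route also needs the full gap at the lowest doses. It cannot cover EC50, which is one value per woman and site, or vessel and gland size, a primary outcome analysed by one-way ANOVA.

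Third, the study is observational, will report confidence intervals and already admits limited power. All true, and the word particularly does not exclude larger differences. Still, the 0.9 claim at 1 SD is left uncorrected.

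**Conclusion.** Wrong as written. For two independent groups of 12, an effect size of 1 does not give power 0.9 at a conventional alpha. Read as a standardised mean difference and tested with a two-sample t-test, the power is about 0.65 (two-sided 5%) or 0.77 (one-sided 5%), a shortfall of about 25 or 13 percentage points. Under the two-sided reading, 12 per group has 90% power only for about 1.39 SD.

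Three stronger readings are not supported:

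- That the power is really 0.46 after Bonferroni, or 0.56 after withdrawals. The adjustment is attached to post hoc comparisons in analyses called exploratory, and no dropout rate is given. The no-replacement rule means only that losses would lower power by an unknown amount.
- That a paired formula was used by mistake. The near match at 0.883 is suggestive, but the article does not say so and the finding does not depend on it.
- That the premenopausal group needs a calculation of its own. Matching a third group to the size of the other two contradicts nothing in the plan.

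**What to change.** Keep n = 36 and revise the Sample size calculation section:

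- State alpha, sidedness, test, effect-size metric and the outcome to which the figure applies.
- If a two-group comparison was intended, restate the result, for example: 12 women per group give about 65% power for a standardised difference of 1.0, and 90% power for about 1.39 (two-sample t-test, two-sided 5%).
- If a repeated-measures calculation was used, say so, give the number of doses and the assumed within-woman correlation, and limit the 0.9 claim to that outcome.
- Amend Study limitations to say that power is limited even for a 1 SD difference in outcomes with a single value per woman, such as EC50 and the biopsy measures.

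Any figure for Bonferroni adjustment or withdrawals should be labelled as an illustrative assumption. The cost is a few sentences and a less favourable stated power. No participant, procedure or analysis changes.

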### Eligibility criteria

Potential participants will exclude themselves based upon the detailed inclusion/exclusion criteria (Table 1) provided on recruitment material and the PIS. These criteria reflect the practical requirements of the study, to ensure that research findings are valid and to ensure the safety of participants. Participants will be consented and screened, consisting of medical history and details of current medications. Postmenopausal participants will complete a 7-day hot flush diary (25). Members of the research team will review completed screening information to confirm eligibility to participate.

**Table 1 T1:** Detailed inclusion and exclusion criteria.

Detailed inclusion criteria		
Postmenopausal + Hot Flush	Postmenopausal	Premenopausal
• Female • Aged 45–65 years • Amenorrhoeic for >6 months • >4 Hot flushes per day • Not on medication or treatments to alleviate hot flushes e.g., HRT	• Female • Aged 45–65 years • Amenorrhoeic for >6 months	• Female • Aged 18–40 years • Eumenorrheic
AND		
• Healthy • Non-smoker/non-vaper • BMI 18–30 kg/m^2^ • No history of cardiovascular or respiratory disease • No history of metabolic diseases e.g., type II diabetes • Drink <14 units of alcohol per week • Participant is willing and able to give informed consent for participation in the study.		
Detailed exclusion criteria		
• Cannot readily read and understand English • Aged <18 years, 41–44 years or >65 years • Male • Current smoker/vaper • BMI <18 or >30 kg/m^2^ • Medical history of cardiovascular/respiratory disease • Medical history of metabolic disease e.g., type II diabetes • Drink >15 units of alcohol per week • Vaccination (<1 week) due to induced systemic inflammatory reaction • Local forearm infection • Allergy to local anaesthetic/Marcaine/amide-group anaesthetics • Currently pregnant, or planning on becoming pregnant • <6 Months postpartum or stopped breast feeding <1 month before recruitment • On medication or treatments to alleviate hot flushes or have taken such medication/treatments within the previous 6 months e.g., HRT		

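### The flush versus no-flush contrast is open to confounding by age and years since menopause: the criteria do not balance them and the stated models do not adjust for them, though direction and size are unknown

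*Protocol article*

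**What the plan says.** Table 1 (Eligibility criteria) gives both postmenopausal columns the same age and menopause entry, "Aged 45–65 years • Amenorrhoeic for >6 months". Age is bounded at 65. Time since the last period has a floor and no ceiling. The hot-flush column adds a minimum of more than 4 flushes a day and no treatment for them. The article mentions no matching, banding or other balancing of the two groups.

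The Sample size calculation rests on previously reported "differences in post-ganglionic skin blood flow responses between postmenopausal women with and without hot flushes", so this is the contrast on which the study was sized.

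For function (Visit 1), the stated model is an exploratory linear mixed model with fixed effects of dose and/or group. For structure (Visit 2), it is a one-way ANOVA. Neither names age or menopausal history. Secondary outcomes lists age among the data collected; years since menopause is not listed.

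On background, the Introduction says that hot flushes affect about 80% "of women for up to several years", and that "the number of skin blood vessels can decrease with aging". The Discussion gives, as an example of what the study might show, greater responsiveness in women with flushes. Study limitations covers the observational design, sample size, single region, diary reporting, single biopsy and single-time sampling. It does not mention age or time since menopause as differences between the two postmenopausal groups.

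**The concern.** If flushes fade over some years, selecting women with more than 4 a day favours those nearer menopause. Selecting women without flushes may favour those whose flushes have ended. The two groups could then differ in age and in years of oestrogen deficiency as well as in flushing. The article itself names ageing and oestrogen withdrawal as causes of change in the skin. An unadjusted difference between the groups would mix these influences with any association with flushes.

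The article says the study will examine whether function or structure is related to the occurrence of flushes. Depending on the sign of the age effect, confounding could create such a relationship or hide a real one. Unlike the premenopausal and postmenopausal age ranges, which do not overlap (18–40 against 45–65), the two postmenopausal ranges are identical. The imbalance can therefore be limited in recruitment and adjusted for in analysis.

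**Working it through.** **The plan's own figure.** The article gives "a power (1-β) of 0.9 and an effect size of 1" and "24 postmenopausal women (12 who experience hot flushes and 12 who do not) and 12 premenopausal women will be recruited". Read as a standardised difference of 1 between two independent groups of 12, with two-sided alpha 0.05 (not stated in that section; assumed in line with the 95% intervals), the noncentrality is 1 × √(12/2) = 2.449 on 22 degrees of freedom. Power is 0.65, so the stated 0.9 is not reproduced; it would need 23 per group. That is a separate matter. Here it supplies only the scale (SD = 1), the group size and the benchmark effect.

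**Inputs the article does not give.** It reports no age SD, no expected age gap and no correlation between age and outcome. Assumed ranges: within-group age SD s = 4–6 years; within-group correlation r = 0.2–0.5; gap in mean age D = 2 or 5 years. For orientation, ages spread evenly over 45–65 have SD 20/√12 = 5.77. The standard error of a difference in mean age is then 5.77 × √(2/12) = 2.36 years, so chance alone gives a 95% range of about ±4.6 years. Chance imbalance is not itself confounding, but it shows that gaps of a few years are ordinary at this sample size.

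**Formulae.** With no true flush effect, the spurious difference in outcome SD units is b = r × D / s. The rejection rate of a two-sided 5% t-test comes from the noncentral t distribution with 22 degrees of freedom and noncentrality b × √6.

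| Gap D | r, s | b | Noncentrality | Rejection rate |
|---|---|---|---|---|
| 2 years | 0.2, 6 | 0.07 | 0.16 | 5.3% |
| 2 years | 0.5, 4 | 0.25 | 0.61 | 9.0% |
| 5 years | 0.2, 6 | 0.17 | 0.41 | 6.8% |
| 5 years | 0.3, 5 | 0.30 | 0.73 | 10.8% |
| 5 years | 0.5, 4 | 0.625 | 1.53 | 31% |

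If the sign ran the other way, the same b would be subtracted from a real effect. With a 5-year gap, a true difference of 1 would on average be estimated as 0.83 down to 0.375.

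**Direction, from the article's own statements.** The Introduction supports a fall in vessel number with age. Fewer vessels in older controls would make the flush group look better supplied, which favours the hypothesis for that measure. No statement says that conductance or sweat responses fall with age. The Introduction also suggests that oestrogen deficiency may affect receptor sensitivity so that blood-flow increases become larger. Longer deficiency in controls could then act against the hypothesis.

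**Cost of adjustment.** For a comparison of 12 with 12 adjusted for age (21 degrees of freedom), the variance inflation from a standardised age gap g is 1 + 6g²/22, and the noncentrality at a true difference of 1 is √6 / √(inflation × (1 − r²)).
- g = 0: power 0.65 at r = 0, rising to 0.77 at r = 0.5.
- g = 1 (inflation 1.273): power 0.54 at r = 0, rising to 0.67 at r = 0.5.

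With balanced ages the covariate costs almost nothing and may gain power. With a large age gap it costs precision, which is the argument for some balance in recruitment.

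**The case against.** The strongest reply has four parts.

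1. **The article is condensed and the statistical analysis plan is not shown.** Covariate lists are commonly left to that plan, the mixed model is called exploratory, and age and oestradiol are collected, so adjustment remains possible. This stands in part: a missing covariate list alone would be no finding. But the article does name its models, and as named they are unadjusted. A later analysis plan cannot change who was recruited. Nor can it use a date of last period that was not recorded; the screening medical history may capture it, but the article does not list it.

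2. **A systematic gap rests on one introductory phrase about duration.** This also stands. The phrase makes a gap plausible and says nothing about its size. Who volunteers as a control, partly through menopause support groups, is unknown.

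3. **The study disclaims causal conclusions.** It does, but it still intends to relate function and structure to the occurrence of flushes, and an unadjusted contrast describes that relation poorly if ages differ.

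4. **Matching is costly and may over-correct.** With 12 controls, one centre and 12 months, strict matching on several age and time bands could stall recruitment. The Introduction says vessels diminish in number and size without recurring rises in flow. Years since menopause may therefore partly track years without flushing, and controlling for it could remove part of the contrast of interest. Both arguments stand and shape the fix.

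A reader might also infer that age has no cap; Table 1 caps it at 65, and only time since menopause is open. A reader might infer that most controls will be former flushers, but that needs an assumed stopping rate that the article does not give.

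**Conclusion.** The concern holds in a limited form. The criteria leave age within 45–65 and years since menopause unbalanced between the two postmenopausal groups, and the stated models do not adjust for either. The contrast behind the sample size is therefore open to confounding.

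It is tempting to conclude that the bias runs towards the hypothesis. The article supports that for vessel number only. For blood-flow and sweat responses the direction is not established, and one of the article's own mechanisms could point the other way.

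The size is unknown. Every magnitude above rests on an assumed age gap, age SD and correlation. A 2-year gap leaves the error rate near nominal (about 5–9%); a 5-year gap gives about 7–31%. The upper figure needs the narrowest assumed age spread and the strongest assumed correlation. This is worth correcting because correction is cheap, not because a serious bias has been shown.

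**What to change.** - At the existing medical-history screen, record the date of the last period for every postmenopausal participant.
- In the with/without comparison, include age as a covariate for function (a fixed effect in the mixed model) and structure (ANCOVA in place of one-way ANOVA). Confine this to the two postmenopausal groups, since the premenopausal ages do not overlap with theirs.
- Repeat the comparison with years since last period as a sensitivity analysis only, given the risk of over-correction.
- Where volunteers allow, keep the two groups' age distributions similar during recruitment, for example with two broad age bands. Strict multi-cell matching is not warranted with 12 controls.
- Report the distributions of age and years since last period in both groups beside any conclusion about hot flushes.

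The cost is one screening question, one degree of freedom, some loss of precision if ages differ (power at a true difference of 1 of about 0.54–0.67 with a 1-SD age gap, against 0.65–0.77 with balanced ages), and possibly slower control recruitment. Broad bands leave some residual confounding. No extra participants or procedures are needed.
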